## Abstract

**Background:**

Anxiety is a common concern of cancer survivors during the transition from active cancer treatment to cancer survivorship (the re-entry phase). This paper presents the study protocol for a novel group-based behavioral intervention to improve mental health, well-being, and medical use outcomes among anxious cancer survivors at re-entry.

**Methods/Design:**

This two-armed, prospective randomized controlled trial will randomize a minimum of 100 re-entry-phase cancer survivors with moderate to high anxiety to the intervention or a usual care control condition. The intervention is delivered in a group format over 7 weeks; content is based on Acceptance and Commitment Therapy (ACT), an acceptance, mindfulness, and values-based intervention. Participants will be recruited from community cancer care centers and the intervention will be led by the onsite clinical social workers. Participants will be assessed at baseline, mid-intervention, post-intervention, and 3- and 6-month follow-up. ACT participants will complete process measures before the beginning of group sessions 2, 4, and 6; all participants will complete the process measures during the regular assessments. The primary outcome is anxiety symptoms; secondary outcomes include anxiety disorder severity, fear of recurrence, depressive symptoms, cancer-related trauma symptoms, sense of life meaning, vitality/fatigue, and medical utilization.

**Discussion:**

This clinical trial will provide valuable evidence regarding the efficacy of the group ACT intervention in community oncology settings.

**Trial registration:**

Clinicaltrials.gov NCT02550925.

## Background

In the United States alone, there are over 15 million cancer survivors, representing nearly 5% of the total population. This number is projected to increase to over 20 million cancer survivors by 2026 [1]. A significant minority of cancer survivors report elevated levels of distress (see [2, 3]). Among various sources of distress, multiple studies suggest that one of the most common psychological concerns among cancer survivors is anxiety [3–6]. Fear of cancer recurrence is the most frequently cited source of anxiety, but the focus of anxiety extends beyond it to encompass additional domains, including anxiety about the effects of treatment and the ability to function in the face of enduring side effects, existential threats to one’s identity or sense of security, financial anxieties in the face of mounting medical bills, fear of investing in the future, and so forth [6, 7]. This study will assess the efficacy of a novel, theory-driven group intervention designed to address the psychological needs of anxious cancer survivors during the transition from cancer patient to post-treatment survivor (the re-entry phase)*.*

Anxiety can be particularly intense during the re-entry phase [6, 8, 9]. At re-entry, cancer survivors prone to anxiety may experience uncertainty about the meaning and purpose of their lives following cancer. Additionally they may worry: ‘Does this symptom mean that my cancer is back?’, ‘How can I live knowing that my cancer might return?’, or ‘Now that treatment is over, will my doctor abandon me?’ [6, 7, 9].

Elevated anxiety predicts the overutilization of oncology care [10] and primary care [11, 12], as well as dose delays or reductions of chemotherapy [13], lower quality of life [14–17], and possibly breast cancer recurrence [18] and earlier death following recurrence [19], though the latter findings are mixed. More broadly, elevated anxiety is linked to elevated risk for full-blown anxiety disorders [20], major depression and depressive symptoms [21], and fatigue [22]. A core symptom of anxiety disorders and elevated anxiety is behavioral avoidance of former activities and associated places, and intrusive or uncontrollable worry [23], each of which can diminish sources of daily meaning such as engagement with social, work, and family life.

For a large minority of cancer survivors, elevated anxiety persists for a decade or more following cancer treatment [3, 4], representing the largest psychological difference between long-term cancer survivors and controls [3, 24–26]. Addressing anxiety early in cancer survivorship—at re-entry, as presently proposed—thus serves a dual purpose: to ease acute anxiety during the often-challenging re-entry phase and to prevent the development of chronic, debilitating, and costly anxiety [3, 27, 28].

### Studies to date

The few prior anxiety-related interventions have focused on fear of recurrence [29–31] or uncertainty in later survivorship phases [32]. These interventions have taken a cognitive behavioral (CBT) or acceptance-based behavioral approach; randomized trials have shown that they significantly reduce fear of cancer recurrence relative to usual care [33], relaxation training [34], and supportive-expressive group therapy [29, 31]. Thus, CBT and related behavioral approaches have a successful track record of reducing fear of cancer recurrence.

Strong evidence demonstrates that cancer patients with higher levels of anxiety and distress benefit most substantially from psychosocial interventions, relative to their less distressed counterparts [35–37]. Yet except for a single study targeting distressed re-entry phase cancer survivors [38], the interventions developed for re-entry phase cancer survivors [39–48] target general cancer survivors rather than the anxious or distressed survivors most in need of help. This study represents one of the first interventions to focus on cancer survivors who report significant anxiety at reentry. By directing resources towards the cancer survivors most in need of support, and by focusing on the psychological symptom (anxiety) that is most likely to become chronic [3–5], the current approach represents an efficient use of psychosocial resources.

### The current intervention approach

The current intervention is founded on a theory-driven, evidence-based behavioral approach, Acceptance and Commitment Therapy (ACT), with demonstrated efficacy for treating anxiety [49–53]. In keeping with the ACT model [54–56], the intervention teaches anxious cancer survivors to: i) cultivate awareness of avoided thoughts and emotions about cancer; ii) disentangle from rigid, limiting thoughts and beliefs about themselves and their experience of cancer; and iii) commit to pursue meaningful life activities aligned with personally held values. According to the ACT model, these processes increase psychological flexibility – the capacity to focus on present-moment experience and to pursue personally valued life directions, even in the presence of internal discomfort (e.g., challenging emotions, physical pain, negative memories) [55–57].

ACT represents a potentially important paradigm shift for addressing anxiety and broader distress among cancer patients and survivors in that it allows for rather than minimizes the distress of cancer and fear of recurrence—an approach that may better validate the fears of re-entry phase cancer survivors, many of whom live with the real possibility of relapse and early mortality. In addition, beyond working to alleviate anxiety and fear of recurrence, ACT helps patients to explore personal values and sources of meaning, addressing the broad existential concerns of many cancer survivors [7, 58] and motivating movement in meaningful life directions.

Our pilot study for anxious cancer survivors at re-entry showed that relative to a one-month baseline period, ACT led to substantially reduced anxiety, depressive symptoms, and fear of recurrence, as well as increased vitality (i.e., lower fatigue) and sense of life meaning [59]. ACT thus helped anxious cancer survivors to increase their capacity to live meaningfully and effectively even *with* side effects and uncertainty about the future. Paradoxically, validating and actively accepting cancer-related distress also reduces it, as shown in this pilot study and in ACT studies with cancer patients during treatment [59–61]. Although not all trials have shown differences between ACT and traditional cognitive behavioral therapy (CBT) [62], a randomized trial for women with late-stage ovarian cancer showed that ACT, despite its lack of focus on symptom reduction, led to lower anxiety and higher quality of life than CBT by large and significant effect sizes [61].

We designed and piloted the current ACT intervention, known as “Valued Living for Cancer Survivors”, in close collaboration with community oncologists and social workers to meet the needs of community-based cancer clinics. First, rather than focus narrowly on a single diagnostic group, Valued Living includes patients across cancer type, an approach that is more sustainable and scalable, according to our community partners. In contrast, most psycho-oncology interventions target a single cancer type or cluster (e.g., breast cancer survivors, colorectal cancer survivors), that is unsustainable for care settings that lack the resources or participants to sustain distinct, intensive interventions for each major cancer type. Second, Valued Living intervenes at the group rather than individual level, representing an efficient use of psycho-oncology resources. Third, the Valued Living group facilitator manual was designed for efficient implementation by community oncology social workers by limiting the number of sessions and by focusing on a few core metaphors, thus enhancing dissemination potential even for psychosocial oncology professionals with limited ACT training. Fourth, the Valued Living groups are led by onsite oncology clinical social workers by leveraging part of their current role (to lead cancer support groups) in the study (to lead Valued Living groups). By contrast, many psycho-oncology interventions are designed and implemented using models or staffing that may not be sustainable in community settings. In that up to 85% of U.S. cancer patients are treated in the community, this approach aims to produce a protocol designed for dissemination in the community settings where the majority of cancer patients receive care.

### The current study

This study will assess the efficacy of Valued Living, a well-piloted ACT group intervention designed to address the psychological needs of anxious cancer survivors during the transition from cancer patient to post-treatment survivor (the re-entry phase). As noted, this trial addresses a number of limitations from previous trials in re-entry phase cancer survivors, first, by targeting anxious cancer survivors rather than cancer survivors generally; second, by adapting an evidence-based behavioral intervention model (ACT) to address the psychosocial needs of anxious cancer survivors; third, by collaboratively designing the intervention with community providers for sustainability in community-based cancer care settings.

Valued Living will be compared to an enhanced usual care control (UC)*.* This study thus aims to determine whether ACT improves outcomes for anxious cancer survivors beyond any benefits realized by usual care. More specifically, we will evaluate the hypothesis that ACT will improve psychosocial functioning by reducing negative effects such as anxiety symptoms (primary outcome), anxiety disorders, intrusive impact of cancer, fear of recurrence, and depressive symptoms, and by increasing positive effects such as appropriate medical care utilization, sense of life meaning, and vitality, relative to the UC control group. Second, to better understand how the group ACT intervention works, we will explore the active therapeutic processes that predict subsequent improvement in outcomes, including change in experiential avoidance and values-driven behavior.

## Methods/Design

### Study design

This two-armed, prospective randomized controlled trial (RCT) will randomize a minimum of 100 anxious re-entry-phase cancer survivors to group ACT (the Valued Living intervention) or a UC control condition. Participants will be randomized on a 1:1 ratio to ACT or UC using a computer-generated block randomization sequence done by a consulting biostatistician who is otherwise uninvolved in the study. All participants will be assessed at 5 points: baseline (Pre), mid-intervention (Mid), post-intervention (Post), and 3- and 6-month follow-up (3 m and 6 m FU). The Post assessment will occur 1 week after the final group session and the 3 m and 6 m FU will occur 3 and 6 months after Post. In addition, ACT participants will complete process measures before the beginning of group sessions 2, 4, and 6; all participants will complete the process measures during the regular assessments as well.

We considered alternative study designs such as comparing Valued Living to a more active condition, including an alternative psychosocial intervention or single educational session. However, in that this study reflects the first randomized trial of Valued Living, comparison to a staff-demanding condition or one that had not yet been empirically evaluated in the community oncology setting of the study, appeared premature.

### Study eligibility criteria

#### Inclusion criteria include

Adults (age 21+) in the Greater Boulder/ Denver, Colorado area who had cancer and completed primary cancer treatment (surgery, chemotherapy, and/or radiation) at minimum 6 weeks and maximum 24 months before the first group meeting, which approximates the ‘re-entry’ phase of cancer survivorship [8, 63].For solid tumor cancers: Show no current evidence of disease for solid-tumor cancers (of any cancer type or initial stage). For lymphoproliferative disorders such as chronic lymphocytic leukemia and indolent non-Hodgkin’s lymphoma: The cancer is in remission or asymptomatic after initial treatment and patients are followed with active surveillance (“watchful waiting”).Screen positive for anxiety symptoms on the study screener (see below)Able to speak, read, and write English fluentlyWilling and able to participate in the study, including completing online questionnaires and phone interviews at designated assessment points and if randomized, completing a group once a week for 7 weeks

#### Exclusion criteria include

Current moderate to high suicide riskPsychiatric hospitalization or suicide attempt in the past 5 yearsHistory of chronic untreated trauma (unrelated to cancer)

### Patient recruitment and consent

Cancer survivors will be recruited primarily from the greater Denver and Boulder metropolitan area offices of Rocky Mountain Cancer Centers (RMCC), the largest network of community oncology practices in Colorado. Patients will be recruited by flyers, targeted mailings, select local media ads, and referrals from survivorship visits with RMCC social workers, advanced practice providers, and medical oncologists. RMCC social workers will consent interested patients to have their contact information released to the University of Colorado research team or will have patients contact the research team directly. With these patients as well as those who self-refer in response to study flyers or media postings, the University of Colorado research team will conduct a final screening to assess all eligibility criteria and explain the details of study participation. Non-RMCC patients, if they learn about the study through a flyer or media posting, will also be eligible and will contact the research team directly to learn more about the study and for eligibility screening. RMCC medical providers will not consent patients to the study.

Following eligibility screening, the research team will send interested, eligible patients a written informed consent form. Patients will be encouraged to read it carefully, given the opportunity to review the consent form and address study-related questions with the research team, and given adequate time to consider whether they would like to voluntarily participate.

### Study conditions

As noted, participants will be randomized to either UC or ACT (the Valued Living intervention) on a 1:1 ratio.

#### Usual care control

Usual Care (UC) will consist of mailing each patient a list of oncology support group resources specifically tailored to each geographic area of recruitment. UC participants will also be encouraged to contact their RMCC social worker (or if they are not RMCC patients, the social worker at their cancer care center) for individual support as needed. UC is designed to provide ethical care for anxious cancer survivors using standard social worker time and resources. In both conditions, we will ask participants to report use of outside supportive and mental health resources on their medical trackers (see below) to account for their use in the analyses.

After the 6-month follow-up (i.e., the final assessment point), UC control participants will be offered the opportunity to participate in an ACT group (free of charge), thus maximizing potential study benefits for all patients. The data from these additional groups will not be included in the primary analyses because we risk confounding the data by comparing cancer survivors at different time points from re-entry and screening, and because we expect that not all UC participants will elect to complete the ACT group. By offering ACT to UC control participants as a benefit of follow-up completion, we aim to enhance patient care without confounding the data.

#### Valued living intervention

The ACT group intervention known as “Valued Living” will consist of 7 weekly group sessions of 2 h each. The Valued Living groups will meet at participating RMCC offices in group rooms appropriate for this purpose. In addition, participants randomized to Valued Living will be mailed the same list of geographically-tailored oncology support group resources that are mailed to participants randomized to usual care.

The Valued Living intervention is based on a facilitator manual and accompanying participant workbook developed during our single-arm pilot study [59]. In the pilot study, we developed and refined a flexible Valued Living manual based on a multi-step process of soliciting feedback from participants, social work group facilitators, and outside ACT experts. In response to their collective feedback, we iteratively refined the manual, including the overall intervention length, session length, and content.

During the first few group sessions of Valued Living, we introduce and use the Matrix [64], a simple tool to teach core ACT skills including increasing awareness of the link between internal experience and external behavior, personal values and their expression in daily life, and various forms of avoidance and their workability in the short- and long-term. In completing the Matrix, we ask group members to discuss their challenging thoughts and feelings related to cancer and the actions they take to get rid of or escape those feelings (struggle actions). We next have them share who and what are most important to them (values) and what they do when they feel connected to their values (valued actions). Whenever challenging cancer-related thoughts and feelings arise, we have them track their responses, and specifically what they do that moves them towards versus away from their values (or a mix of both).

In the middle Valued Living sessions, participants learn how to respond skillfully to cancer-related concerns and feelings and move towards valued actions, rather than remain stuck in struggle actions. A central tool in these sessions is the Passengers on the Bus metaphor [55], which invites participants to identify persistently challenging thoughts and images about cancer, labeled ‘passengers’. We physically enact this metaphor in the group. In doing so, we practice how to actively accept, and flexibly and compassionately relate to passengers while reducing their dominance over participants’ lives.

The final sessions of Valued Living focus more intensely on helping participants clarify their own values and a sense of purpose beyond, or even in the midst of, the threat of cancer. Participants also then focus more on committing to behaviors in alignment with those values, and on cultivating compassion for themselves in that process.

### Intervention training and facilitation

Participating RMCC offices have onsite clinical social workers who have expressed interest in learning ACT. Authors [name] and [name] train them in the ACT approach and the Valued Living protocol over 3 days, with 1 day of training every ~ 2 weeks to allow for readings and home practice between training days and to accommodate their clinical schedules. The training days incorporate active role-playing, experiential exercises, and coaching, followed by weekly feedback-based supervision, approaches recommended by the empirical literature [65, 66]. Second, an RMCC clinical social worker experienced in ACT co-facilitates the Valued Living groups, providing additional mentoring and consistency in the delivery of the intervention.

### Study ethics and integrity

Ethics approval was received from the University of Colorado Boulder Institutional Review Board (IRB) and Rocky Mountain Cancer Centers (RMCC); the University of Colorado Cancer Center approved the study protocol. Written informed consent will be obtained from all study participants. The University of Colorado has the right to audit the study. Protocol modifications will be submitted to the University of Colorado Boulder IRB and the University of Colorado Cancer Center. This is the second protocol version submitted to clinicaltrials.gov, dated July 27, 2018, reflecting the addition of anxiety disorder severity as a secondary outcome. Given the modest sample size and scope of the study, and the low-risk nature of the intervention, the study team did not elect to have a data monitoring committee. Any adverse study events will be reported to the University of Colorado Boulder IRB in a timely manner.

All participants will be assigned and referred to by their participant ID number to protect their identities. Participants’ names and ID numbers will only be linked in one secure, password-protected document stored separately from their demographic information or study data. Data will be entered into secure, password-protected databases stored on an encrypted external hard-drive in a locked research office. A separate research team member will verify all hand-entered data and check for participant entry errors for Qualtrics-collected data to help ensure the accuracy of the data. Participants will complete the baseline assessment before randomization to study condition. The principal investigator (PI), data analysts, and research team members conducting the outcome assessments will remain blind to condition assignment. Blindness for these team members will be achieved by not discussing condition status with the unblinded study coordinator, not attending the Valued Living groups, not rating videotaped sessions for fidelity (see below) until after the final assessment is conducted, and requesting during diagnostic assessment interviews that participants not reveal their assigned condition (see Anxiety Disorder measures, below). The CONSORT statement guidelines [67] inform the trial design throughout.

To implement the computer-generated block randomization sequence (see Study Design), the unblinded study coordinator will assign participant ID numbers in the consecutive order in which participants consent, and then link the list of ID numbers for each cohort to a spreadsheet column next to a hidden column of the block randomization sequence. The unblinded study coordinator then will unhide the sequence to determine which participant IDs are allocated to each condition in the ID sequence. The unblended coordinator will communicate condition assignment to participants and will videotape the group sessions and schedule the groups with the onsite social workers. Research team members experienced in ACT, none of whom run the Valued Living groups, will rate 2 randomly selected videos per group (~ 30% of sessions) for fidelity to the manual. They will rate only after extensive training to achieve respectable inter-rater reliability.

The PI can become unblinded to a participant’s study condition by the unblinded study coordinator in order to assess for potential clinical deterioration or emergency, such as in the case of patient-reported or indicated suicidality (assessed in the diagnostic interview, see Anxiety Disorder measures). Participants also can be withdrawn from the study at the PI’s discretion for reasons such as arriving to a group session inebriated or high, or exhibiting disruptive behaviors in group, e.g., yelling at or shaming other group members. To account for such occasional cases, participants will generally be discussed on the basis of their participant ID numbers for study purposes and will be discussed by first name in cases of potential clinical deterioration or study disruption; thus, if the name of a participant is revealed for purposes of PI assessment, then the PI will still remain blind to the participant’s ID number in the study database.

Study results will be communicated by submission to a peer-reviewed journal for publication and reporting of results in clinicaltrials.gov.

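### Allocation concealment is not secured against the unblinded coordinator, who numbers participants, works in the file holding the hidden sequence and unhides it

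*Protocol article*

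**What the plan says.** Under Study design, the article describes a "computer-generated block randomization sequence done by a consulting biostatistician who is otherwise uninvolved in the study", with a 1:1 ratio. Generation is therefore independent of the study team.

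Under Study ethics and integrity, the sequence is put into use by one person, in four steps:

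1. Numbering: "the unblinded study coordinator will assign participant ID numbers in the consecutive order in which participants consent".
2. Linking: the coordinator is to "link the list of ID numbers for each cohort to a spreadsheet column next to a hidden column of the block randomization sequence".
3. Revealing: "The unblinded study coordinator then will unhide the sequence to determine which participant IDs are allocated to each condition in the ID sequence".
4. Telling: "The unblended coordinator will communicate condition assignment to participants" (the article's spelling; unblinded is evidently meant).

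The same section says that baseline is completed before randomisation. It describes password protection for the file linking names to IDs and for the study databases, and it lists steps to keep the principal investigator, analysts and assessors blind. It describes no lock, third-party release or audit trail for the sequence.

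**The concern.** Independent generation and allocation concealment are separate safeguards. Generation makes the sequence unpredictable in itself. Concealment keeps it from anyone who can affect who takes which place in it, until that place is fixed. Here the sequence leaves the biostatistician and sits in the working file of the person who numbers the participants. Anyone with the file can unhide a column and, as the procedure is described, this would leave no record.

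If assignments were seen early, the order or timing of entry could come to depend on the coming arm. The resulting imbalance could be in characteristics that were never measured, and no analysis can remove that part. The exposure matters more here because the primary outcome, HADS anxiety, is self-reported by participants who know their arm. Sound allocation is then one of the main protections of comparability that remain.

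**Working it through.** The article gives no figure on this point, so there is none to reproduce. The check is to compare what the text fixes with what it leaves open.

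**Fixed by the text**
- Sequence generated by an otherwise uninvolved biostatistician (Study design).
- Baseline before randomisation; IDs in consent order; each cohort's IDs placed beside the hidden column; column then unhidden; arm communicated (Study ethics and integrity).
- Numbering, linking, unhiding and communicating are all done by the coordinator (same section).

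**Not stated**
- When the coordinator receives the file containing the sequence.
- Whether the hidden column covers one cohort or several.
- Whether the file has a password or a change log.
- Whether the coordinator takes part in screening or consent. Patient recruitment and consent assigns final screening to the university research team as a whole.

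**Reasoning**
1. If the steps are followed as written, nobody sees an assignment before the cohort's IDs are listed. The intention is concealment.
2. Nothing described enforces that order. A coordinator who already has the file could open the column before the list is final. This holds even if the column covers only one cohort.
3. If the column covers several cohorts (an assumption), carrying out step 3 properly for one cohort would reveal the assignments waiting for the next. No misconduct would be needed for the coordinator to know them.
4. Knowledge matters only if something can be varied. Consent order sets the numbering, but the coordinator turns consents into IDs and no independent time stamp is described. The eligibility window runs from 6 weeks to 24 months after treatment, counted back from the first group meeting, so some people could plausibly enter either of two successive cohorts. That is an inference; the article does not describe how people are placed in cohorts.

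**Hypothetical scale**
- Inputs: 50 per arm and a planned effect of d about 0.50 (Power and sample size estimation). Five exchanged pairs and a prognostic gap of 1 SD within each pair are assumptions with no support in the article.
- Shift in each arm's mean: 5 × 1 SD / 50 = 0.1 SD, in opposite directions.
- Shift in the between-arm difference: 0.1 + 0.1 = 0.2 SD.
- Relative to the planned effect: 0.2 / 0.50 = 40%.

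The shift is proportional to both assumed inputs: one pair at 1 SD gives 2 × 1/50 = 0.04 SD, and five pairs at 0.5 SD give 2 × 2.5/50 = 0.1 SD. This shows sensitivity. It does not estimate what happened.

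**The case against.** The strongest reply is that the procedure does conceal allocation. Consent and baseline come first, numbering follows consent order rather than choice, the cohort list is set beside a hidden column, and only then is it opened. The sequence itself comes from an independent source. A condensed article may also omit file protection that was in place. All of this stands, except that a stated order of steps does not secure concealment when the person bound by it holds the file.

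Some stronger readings are tempting but unsupported:

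- **That allocation is simply not concealed.** A reader might infer this from the hidden column. The written order of steps contradicts it.
- **That later cohorts were exposed.** This needs a column spanning cohorts. The text links lists cohort by cohort and does not say how far the column runs.
- **That the coordinator could steer eligibility or consent.** The article does not give the coordinator either task, and eligibility rests on listed criteria and numeric screener cut-offs.
- **That coming assignments could be guessed from past ones within a block.** Such calculations assume one-at-a-time allocation. Here a cohort is numbered before any of its assignments are shown, and the article states no block size.
- **That any bias would be beyond repair.** Baseline is measured before randomisation and the analyses plan to include covariates such as age and gender, so imbalance in measured prognosis can be partly addressed. Only the unmeasured part cannot.

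**Conclusion.** The point holds in a limited form. Concealment is intended, but it is not secured against the coordinator, because it depends on that person following the order of steps in a file that already contains the answer. This rests on what the article affirmatively describes together with the absence of any described lock or outside release. It would weaken if the file was in fact protected or was supplied only after each list was final. It would be more serious if the column spans several cohorts.

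The size of any bias is unknown. The 0.2 SD figure is a hypothetical illustration, and nothing in the article suggests that steering took place. The case for change is that the weakness is avoidable at very little cost.

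**What to change.** **Cohorts not yet randomised.** The consulting biostatistician keeps the sequence. When a cohort closes, the coordinator sends a final, time-stamped list of IDs that are consented, eligible and baseline-complete, in consent order. The biostatistician returns allocations for those IDs only, and both messages are kept on file.

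**Cohorts already randomised.** The Measures section mentions a change made midway through the study, so the trial was under way and earlier cohorts cannot be changed. For these, the report should state the method used: who held the file and from when, whether the column covered more than one cohort, and what protection the file had.

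**Cost.** One exchange per cohort with a biostatistician already engaged, a short procedural amendment, and a brief wait for the reply before participants are told their arm. Sample size, assessments and analysis are unchanged.
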